## Abstract

**Introduction:**

The Developmental Origins of Health and Disease (DOHaD) hypothesis proposes that intrauterine and early life exposures significantly influence fetal development and risk for disease in later life. Evidence from prospective birth cohorts suggests a role for maternal B_12_ and folate in influencing neurocognitive outcomes in the offspring. In the Indian setting, B_12_ deficiency is common during the pregnancy while rates of folate deficiency are lower. The long-term influences of maternal nutrition during the pregnancy on adult neurocognitive outcomes have not been examined. The Pune Maternal Nutrition Study (PMNS) is a preconceptional birth cohort into its 24th year and is considered a unique resource to study the DOHaD hypothesis. We found an association between maternal B_12_ status in pregnancy and child’s neurocognitive status at 9 years of age. We now plan to assess neurocognitive function and MRI measurements of brain structural–functional connectivity at young adult age to study its association with maternal nutritional exposures during the pregnancy.

**Methods and analysis:**

As part of ongoing prospective follow-up in young adults of the PMNS at the Diabetes Unit, KEM Hospital Research Center, Pune India, the following measurements will be done: neurocognitive performance (Standardised Tests of Intelligence, Verbal and Visual Memory, Attention and Executive Functions), temperament (Adult Temperament Questionnaire), psychopathology (Brief Symptom Inventory and Clinical Interview on Mini Neuropsychiatric Interview 7.0). Brain MRI for structural T1, resting-state functional connectivity and diffusion tensor imaging will be performed on a subset of the cohort (selected based on exposure to a lower or higher maternal B_12_ status at 18 weeks of pregnancy).

**Ethics and dissemination:**

The study is approved by Institutional ethics committee of KEM Hospital Research Center, Pune. The results will be shared at national and international scientific conferences and published in peer-reviewed scientific journals.

**Trial registration number:**

NCT03096028

Strengths and limitations of this studyInvestigation of structural and functional neurodevelopment of young adults in the Pune Maternal Nutrition Study in relation to intrauterine exposure to vitamin B_12_ and folate.A unique dataset of intergenerational life course exposures (physical growth, nutrition, childhood adversity) to investigate pathways of neurocognitive development.Comprehensive behavioural measures and neuroimaging techniques (structural and functional).Cross-sectional MRI measurements instead of trajectories of brain growth.First life course study in Low and Middle Income Countries (LMIC) to evaluate associations of early life exposures with brain outcomes in adult age.

## Introduction

The Developmental Origins of Health and Disease (DOHaD) hypothesis^1 2^ proposes that early life exposures along with postnatal environmental factors (childhood experiences, education, nutrition, infections, lifestyle, socioeconomic conditions) determine risk for disease in later life. Recent investigations suggest an early life origin of neurodevelopmental disorders (autism spectrum disorders, depression, schizophrenia).^3^ Early intrauterine insults can impact development of brain areas that show high neuronal growth such as hippocampus and cortical areas.^4^ Later life factors influence synaptic pruning and myelination.^5^ Altered brain structural and functional connectivity within and between hippocampal, frontal and subcortical networks is known to be associated with impaired neurocognitive functioning and neurodevelopmental disorders.^6 7^

The growing fetus is wholly dependent on the mother for its nutrition. Deficiency of various micronutrients in the mother during critical phases of fetal development can affect organ structure and function, hence programming the risk for chronic disease in later life (fetal programming).^8^ Recently, there is considerable interest in the role of maternal vitamin B_12_ and folate in fetal programming.

Vitamin B_12_ is important for nerve myelination and its deficiency is associated with subacute combined degeneration of spinal cord, depression and dementia.^9^ The role of folate deficiency in risk for neural tube defects (NTDs) is well known. Both these vitamins influence the one carbon metabolism cycle.^10^

Observations from large prospective cohort studies such as the Norwegian mother and child birth cohort^11^ and Generation R support association of poor maternal folate status with poorer neurocognitive functioning, greater childhood behavioural problems,^12–14^ smaller brain volumes^15^ and risk for autism.^16 17^ Prospective cohort studies from India support the associations of lower maternal vitamin B_12_ or folate with higher risk for NTD and poorer cognitive functions in offspring in early (30–48 months) and late (9–10 years) childhood. Systematic reviews support a high level of evidence for association of low maternal vitamin B_12_ with high risk for NTD and moderate level evidence for poor cognitive outcomes in the offspring.^18 19^ It must be noted that these observational studies do not support causality. Causality can be examined by randomised controlled trials, which need time and involve ethical considerations. Techniques such as Mendelian randomisation allow testing for causality of observed associations.^20^ The Avon Longitudinal Study on Parents And Children reported association between low maternal dietary intake of vitamin B_12_ and lower IQ scores at 8 years and genetic determinants of vitamin B_12_ (FUT2gene) using this technique.^21^

In India, vitamin B_12_ deficiency is widely prevalent in women in the reproductive age group while rates of folate deficiency are low.^22–24^ The vitamin B_12_ deficiency is attributable to practice of vegetarianism and low socioeconomic status. Public health policy mandates only iron-folic acid supplementation in adolescents and pregnant women. It is also a common clinical practice to supplement high dose folic acid (5 mg) to pregnant women to prevent NTD. This scenario inadvertently promotes an imbalance between vitamin B_12_ and folate status during the pregnancy,^19 25^ which could enhance risk of adverse health outcomes in the offspring including aberrant neurodevelopment. In the presence of vitamin B_12_ deficiency, folate is trapped in its unusable methyl form and methyl groups are unavailable for further biochemical reactions. This interferes with important cell processes such as purine pyrimidine synthesis, DNA repair and epigenetic regulation (DNA methylation). Unavailability of methyl groups prevents conversion of homocysteine to S-adenosyl methionine leading to hyper-homocysteinaemia which can adversely affect vascular endothelial and placental function. Indiscriminate supplementation in the presence of vitamin B_12_ deficiency leads to accumulation of unmetabolised folic acid, which is known to have neurotoxic effects.^25 26^ Animal experiments performed in India have examined the role of a maternal vitamin B_12_-folate micronutrient imbalance and show that offspring dams of mothers fed on a low vitamin B_12_-highfolate diet have poorer spatial memory functions, lower brain hippocampal weight, reduced neurotrophic factor BDNF and reduced TRK gene expression.^27 28^ However, no study in India has examined long-term effects of maternal vitamin and folate during the pregnancy on offspring neurodevelopmental outcomes in young adulthood.

The Pune Maternal Nutrition Study (PMNS) is a preconceptional birth cohort with serial data on maternal nutritional status, birth outcomes and offspring nutrition, physical growth and development. We have observed high prevalence of maternal vitamin B_12_ deficiency during the pregnancy in our cohort. We have described markers of low vitamin B_12_ status in the mother (high homocysteine) to be causally associated with low birth weight in the offspring.^29^ A low vitamin B_12_-high folate dietary pattern was associated with adverse metabolic outcomes in the offspring at 6 years.^24^ We have earlier demonstrated in this cohort that exposure to a low maternal vitamin B_12_ was associated with poor cognitive functioning in the offspring at 9 years of age.^30^ The offspring of this cohort is now in their early 20s and this provides a unique opportunity to examine the long-term effects of maternal nutrition status during pregnancy on neurocognitive outcomes in young adulthood.

### Aims and objectives

The key aim of the study is to examine whether maternal micronutrient status during pregnancy (B_12_, folate) is associated with neurocognitive performance, structural and functional connectivity and risk for common mental disorders in young adult offspring of the PMNS birth cohort.

Primary objectives

To examine associations between maternal vitamin B_12_, folate and their interaction at 18 and 28 weeks of pregnancy with neurocognitive outcomes (neuropsychological test performance) and risk for common mental disorders (temperament, presence of depression or anxiety disorders) in young adulthood; controlling for the effects of other nutrients (calorie, protein and fat intake, and levels of vitamin C, D, ferritin) and later life developmental influences (education, adverse childhood experiences (ACE), offspring nutrition, physical growth and development, metabolic status).To examine the association of maternal nutritional status during the pregnancy with brain structure (grey matter volume and cortical thickness), and structural/functional connectivity (using diffusion tensor imaging (DTI) and resting state functional MRI (rsfMRI), respectively).To test the causality of association between maternal vitamin B_12_, folate and neurocognitive outcomes using maternal and offspring genetic determinants of vitamin B_12_ (FUT2, FUT6, TCN2).

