## Methods and analysis

### Study setting

#### Pune Maternal Nutrition Study

The PMNS is a preconceptional cohort, established in six villages of Pune district, Maharashtra state, India in 1993 in collaboration with [name] and [name] and is considered a unique resource in the world to examine the DOHaD paradigm. Initially, 2466 women (F0 generation) in the reproductive age group participated in the study. A total of 814 women who became pregnant in the period June 1994 to April 1996 were enrolled for the study. Of these 797 pregnancies (with singleton pregnancy and period of gestation less than 21 weeks) were included. A total of 762 live births occurred (F1 generation). This cohort has data on preconceptional parental size, maternal nutrition and size at birth of the offspring. Maternal micronutrients vitamin B_12_, red cell folate and ferritin have been measured from blood samples collected at 18 and 28 weeks of gestation. Vitamin B_12_ levels were measured using the microbiological assay technique and red cell folate and ferritin by radioimmunoassay.^24 31^ Children are being regularly followed up for growth and development (body size and DXA body composition), nutrition and cardiometabolic risk factors (6, 12 and 18 years of age). Biological samples have been collected and stored in a biorepository and are available for assessments. The other strengths of this cohort are good community participation and follow-up rates of over 90% over the years. At 18 years follow-up, 690 of the original 762 live births in the cohort were followed up.

The participants (F1 generation) of the cohort are also part of a randomised controlled trial (Pune Rural Intervention in Young Adolescents, PRIYA)^32^ to examine intergenerational effects of micronutrient supplementation on various health outcomes. In 2012 at the age of 17 years 557 eligible members were randomised as part of the nutrition intervention trial into 1 of three groups (1) 2 micrograms/day of vitamin B_12_, (2) 2 μg/day of vitamin B_12_ with UNIMAPP multivitamins and 20 g milk powder and (3) placebo. The trial was completed in the boys in December 2017 and in the girls in September 2019. The effects of later life intervention will be adjusted during statistical analysis (figure 1—depicts time line of measurements in the PMNS cohort).

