### Assessments

The exposures and outcome measurements are summarised in table 1.

**Table 1 T1:** Exposures and outcomes defined in the study

	Exposures	Tests	Variables measured
1.	Maternal Micronutrient status and homocysteine at 18 and 28 weeks pregnancy	Biochemical assays	Vitamin B_12_, red cell folate, homocysteine

	Outcomes	Tests	Variables measured
1.	Neurocognitive performance	WAIS-IV WMS AVLT Colour Trails test	Verbal comprehension, perceptual reasoning, working memory, processing speed, Full scale IQ. Immediate memory, delayed memory and working memory. Errors in immediate and delayed recall time taken and errors for colour trails test A and B.
2.	Temperament	Adult Temperament Questionnaire	Negative affect, extraversion, orienting sensitivity, effortful control
3.	Common mental disorders	Brief Symptom Inventory Mini Neuropsychiatric Interview 7.0 for DSM 5 diagnosis	Global severity index DSM 5 diagnosis of past or current major depressive disorder, suicidality, panic disorder, agoraphobia, social anxiety disorder, generalised anxiety disorder
5.	Brain Imaging	Structural T1 MPRAGE Resting state fMRI Diffusion tensor imaging	Cortical volume and thickness Resting state functional connectivity tractography, FA and MD values in relevant white matter tracts
	Life course variables		
	Birth		Birth weight, length, head circumference, sum of skin folds
	Later life growth and development		Height, BMI, head circumference sum of skin folds at 6, 12, 18 years
	Later life nutrition		Haemoglobin, vitamin B_12_, folate, homocysteine, ferritin, glucose, lipids at 6,12,18 years
	Socioenvironmental		Mothers education, fathers education, standard of living index, adverse childhood experiences.

AVLT, auditory verbal learning test; BMI, body mass index; DSM, Diagnositic and Statistical Manual of Mental Disorders; FA, fractional anisotropy; fMRI, functional MRI; MD, mean diffusivity; WAIS-IV, Wechsler’s Adult Intelligence Scale IV; WMS, Wechsler Memory Scale.

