### Data management

Data will be stored at the Diabetes Unit, KEM Hospital Research Center, Pune, India. Data collected will be first entered in a paper clinical record form and double entered into an open clinical platform on a computer. Data will be downloaded and checked for extreme or missing values. Data on maternal micronutrient status during the pregnancy (nutrition intake, circulating micronutrients) and intermediate variables (birth size, childhood nutrition, growth and development, metabolic factors (insulin resistance, glycaemic status, adiposity), sociodemographic variables and socioeconomic status have been assessed previously on the cohort. These will be extracted and used for analysis.

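### The covariate lists do not separate pre-exposure confounders from later-life variables, omit preconception maternal size, and leave socioeconomic status out of the fixed MRI model

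*Protocol article*

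**What the plan says.** **Objective 1.** Under Aims and objectives, the association is to be estimated while "controlling for the effects of other nutrients (calorie, protein and fat intake, and levels of vitamin C, D, ferritin", and also while controlling for "later life developmental influences (education, adverse childhood experiences (ACE), offspring nutrition, physical growth and development, metabolic status". In the Plan of data analysis, the life course variables of Table 1 are brought in as possible modifiers and mediators, and further models may follow from the univariate results.

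**Table 1 (Assessments).** The physical measures in the life course block begin with "Birth weight, length, head circumference, sum of skin folds" and run on to 18 years. The socioenvironmental row reads "Mothers education, fathers education, standard of living index, adverse childhood experiences".

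**Objective 2 (Plan of data analysis).** Age, gender, total intracranial volume and ACEs are regressed out. The offspring's current B12, education and socioeconomic status are additional factors whose effects will be looked at.

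**What the cohort holds.** The section on the Pune Maternal Nutrition Study states "This cohort has data on preconceptional parental size, maternal nutrition and size at birth of the offspring", and that the cohort was "established in six villages of Pune district, Maharashtra state, India in 1993".

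**The concern.** The exposure is maternal B12 and folate at 18 and 28 weeks. A confounder must precede or accompany it; what happens to the child afterwards may lie on the causal path. The lists mix the two kinds, and the same later-life variables are both controlled for (Aims and objectives) and studied as mediators (Plan of data analysis). Controlling for a mediator removes part of the effect sought, while omitting a pre-exposure common cause leaves a spurious part in.

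Maternal size before pregnancy precedes the blood sample, so it cannot mediate the exposure, and it plausibly marks the mother's long-term nutrition and background. The cohort is distinctive for having it, yet no list uses it.

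In the MRI model the gap is plainer. The Introduction attributes B12 deficiency to vegetarian practice and low socioeconomic status, and low socioeconomic status may also affect brain development. No fixed MRI covariate describes the mother or household before the exposure. The Hypotheses are causal and the findings are meant to inform public health action, so the adjusted estimate will be read as more than a description.

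**Working it through.** The document states no figure on this point, so the check is mainly a comparison of passages.

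| Variable | Timing against the 18-week sample | Where it appears | Role given |
|---|---|---|---|
| Preconception parental size | Before | Study setting only | None |
| Village | Before | Study setting only | None |
| Parental education | Largely before | Table 1 | Life course variable (Objective 1); the MRI extra is education, whose is not stated |
| Living standard, socioeconomic status | Date not stated | Table 1, Data management, Objective 2 | Life course variable (Objective 1); extra (MRI) |
| Maternal intake, vitamins C and D, ferritin | Pregnancy | Aims and objectives, Data management | Controlled in Objective 1; absent from MRI |
| Birth size, growth, offspring nutrition, metabolic status | After | Aims and objectives, Table 1 | Growth, nutrition and metabolic status controlled; the Table 1 items also treated as modifiers or mediators |
| ACEs | After | Aims and objectives, Table 1, Objective 2 | Controlled in Objective 1; fixed in MRI |

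The pregnancy timing of the nutrients comes from Data management: "Data on maternal micronutrient status during the pregnancy (nutrition intake, circulating micronutrients". That section also lists the existing data to be extracted. It includes sociodemographic and socioeconomic data but does not mention preconception size.

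**Illustration of size.** All confounder strengths here are assumptions; the document gives none.

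1. Standardised bias = r × β, where r is the correlation of the omitted variable with maternal B12 and β its effect on the outcome. The yardstick is the 0.11 SD per SD under Power estimation.
   - 0.05 × 0.05 = 0.0025, or 2% of 0.11
   - 0.10 × 0.10 = 0.01, or 9%
   - 0.20 × 0.20 = 0.04, or 36%
   - 0.30 × 0.30 = 0.09, or 82%
2. With bias B and no true association, a nominal 5% test at n = 550 rejects with probability Φ(B√n − 1.96) + Φ(−B√n − 1.96). For B = 0.01 this is 5.6%; for B = 0.04 it is 15.5%.
3. Suppose a planned covariate (say, parental education) correlates ρ with the omitted variable and acts only as its proxy. The remaining bias is rβ(1 − ρ²)/(1 − r²ρ²). With r = β = 0.20, the 0.04 becomes 0.037 (ρ = 0.3), 0.030 (ρ = 0.5) or 0.021 (ρ = 0.7).

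Proxies therefore reduce such a bias without removing it. The range in step 1 is so wide that it shows only that the size is unknown.

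**The case against.** The strongest reply is that this is a condensed article. The Objective 1 scheme is described as broad and leaves further models open, and a full covariate list may stand in a plan not shown. That has force for Objective 1, where leaving a variable unnamed is not a decision to exclude it. It has less force for Objective 2, where a fixed set is stated and socioeconomic status is placed outside it.

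Several stronger readings are tempting but unsupported:

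- **That adjustment begins only at birth.** It does not. The nutrients in the first objective are pregnancy measures, and Table 1 has parental education and a living-standard index.
- **That pre-exposure confounding stays in the estimates in full.** The planned covariates may capture part of it.
- **That maternal size or village is a demonstrated confounder.** No passage links either to B12 or folate. The causes of deficiency that the document names are vegetarian practice and socioeconomic status.
- **That ignoring village makes the tests invalid.** No intraclass correlation is given. Assuming six equal villages and the same correlation in exposure and outcome, a 5% test would run at 5.3–5.4% for 0.02 and 6.9–7.7% for 0.05 (n = 386 to 550). That "established in six villages of Pune district" describes the cohort does not show that village is held as an analysable code.

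The Mendelian randomisation in Objective 3 offers a separate route to causality, but for neurocognitive outcomes. It does not cover the MRI comparisons and names no folate score.

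**Conclusion.** The point holds in a limited form. Pre-exposure and post-exposure covariates are not kept apart, preconception maternal size is held but named in no list, and the fixed MRI model omits socioeconomic status, which the document itself names as a cause of the exposure. Confounding may partly remain in Objective 1 and is less well guarded against in Objective 2. Neither its size nor its direction can be set from the document; the percentages in the working rest wholly on assumed strengths. The case rests on the order of events and on the Introduction's own account of B12 deficiency, together with the judgement that maternal size and household circumstances plausibly bear on offspring cognition and brain structure.

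**What to change.** State one fixed pre-exposure set that enters every Objective 1 and Objective 2 model:

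- maternal preconception size (height and weight, or BMI);
- mother's and father's education;
- standard of living or socioeconomic status, using the earliest record and stating its date;
- village of recruitment, maternal age and parity, if these are held.

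Report the maternal B12 and folate estimate with this set first. Add post-birth life course variables, including ACEs, only in later models labelled as mediation or modification. Age, gender and intracranial volume can stay in the MRI model as planned.

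Cost: with linear terms, up to 2 degrees of freedom for size, 2 for parental education and 1 for living standard, so 5. Village adds 6 − 1 = 5, and maternal age and parity 2, giving at most 12. This is set against 386 to 550 participants for Objective 1 and 195 to 200 for MRI. The core set needs no new measurement, though its completeness should be checked before the set is fixed.

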### Hypotheses

We hypothesise that a lower maternal vitamin B_12_, higher folate, higher homocysteine nutrient pattern during pregnancy adversely impacts development of brain regions. This will be reflected in brain imaging as reduced brain volume as measured through anatomical images, weaker connections in structural/functional networks (hippocampal and frontal-subcortical connections) involved in cognitive processing (memory, executive functions) as measured through DTI and rsfMRI, respectively. These structural and functional changes will in turn result in poorer neurodevelopmental outcomes (lower neuropsychological test performance, adverse temperamental traits and higher risk for common mental disorders) in the young adult offspring.’

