### Plan of data analysis

#### Objective 1

This examines the association between intrauterine nutritional exposures and neurocognitive outcomes in young adult age:

Our primary exposure of interest is maternal vitamin B_12_ and red cell folate levels. Due to lack of reliable clinical cutoffs for these micronutrients during pregnancy for our population, we prefer to use the distribution within population to classify participants. Such an approach has been used earlier to report metabolic outcomes in the offspring in this cohort.^24^ Distribution of outcome variables such as neurocognitive performance scores will be visualised by using different plotting techniques such as box plot and scatter plot. Univariate analysis (Pearson’ correlation and linear regression) will be performed to examine the relationships between the primary exposures, life course variables and neurocognitive outcomes (table 1). We expect to construct multivariate linear (if outcome is continuous) or logistic regression (categorical outcome) models to examine associations of our primary exposures with neurocognitive outcomes and extend the models to examine potential modifying and mediating effects of life course variables on the associations. Finally, we will adjust for the vitamin B_12_ intervention status (vitamin B_12_ intervention received yes or no) in the PRIYA trial. We will follow this broad scheme of analysis. Depending on observed univariate associations we may construct additional multivariate models.

Given the multitude of factors and possible collinearity, we will use dimensionality reduction techniques (such as principal component analysis or Lasso). The components might be used to construct path analytical models for exploring associations between outcomes.

#### Objective 2

This examines the association between maternal nutritional exposures and brain structural functional connectivity:

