
For each modality, the following statistical comparisons will be performed. We will first perform correlations between maternal vitamin B_12_ and folate exposures with brain MRI outcomes to examine for any linear relationships. We will use an analysis of covariance model to examine differences in MRI outcomes between low and high maternal vitamin B_12_ groups. Similarly, we will examine for differences between low and high maternal red cell folate groups (selected based on median value of maternal red cell folate) and for any interaction between maternal vitamin B_12_ and folate status. Variance due to subjects’ age, gender, total intracranial volume, ACEs will be regressed out of the analyses. Effects of additional factors (such as current vitamin B_12_ status of offspring, education status, socioeconomic status) will be examined.

For making inferences from multimodal imaging data, we will adopt a hierarchical approach. Accordingly, we will perform voxel-wise tests for difference in grey matter volume (or cortical thickness). For brain regions which are significant, DTI-based structural connectivity and fMRI-based functional connectivity between those regions will be investigated. This strategy assures that the effects of interest have both structural and functional aetiologies, and hence are likely to be robust and reproducible.

#### Objective 3

This examines causality of association between maternal nutritional factors and neurocognitive outcomes. The genetic determinants of vitamin B_12_ have been described in our population using GWAS,^36^ which will be used to calculate a gene risk score of vitamin B_12_ deficiency. Mendelian randomisation analysis (triangulation and instrumental variable analysis) using the genetic risk score for vitamin B_12_ deficiency and homocysteine (MTHFRrs1801133) will be performed.

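### The first primary objective controls for offspring nutrition, growth and metabolic status, which the protocol elsewhere treats as intermediate, and no confounder-only model is named to answer it

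*Protocol article*

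**What the plan says.** Aims and objectives in the protocol article frames the first primary objective as the association of maternal B12, folate and their interaction at 18 and 28 weeks with young-adult neurocognitive and mental health outcomes, "controlling for the effects of other nutrients (calorie, protein and fat intake, and levels of vitamin C, D, ferritin) and later life developmental influences". The later-life part of that list reads "later life developmental influences (education, adverse childhood experiences (ACE), offspring nutrition, physical growth and development, metabolic status".

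Other sections give several of these variables a different role:

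- The Introduction reports, from the same cohort, that "A low vitamin B_12_-high folate dietary pattern was associated with adverse metabolic outcomes in the offspring at 6 years".
- Data management groups birth size, childhood nutrition, growth and development, and metabolic factors as intermediate variables.
- Plan of data analysis, Objective 1, starts with univariate analyses, goes on to regression models for the primary exposures, and will then "extend the models to examine potential modifying and mediating effects of life course variables on the associations".
- Table 1 places head circumference at 6, 12 and 18 years among the later-life growth variables.

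For MRI, the Hypotheses section predicts that the exposure will impair development of brain regions: "This will be reflected in brain imaging as reduced brain volume as measured through anatomical images". Under Objective 2, for each modality, age, "gender, total intracranial volume, ACEs will be regressed out of the analyses".

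**The concern.** Offspring nutrition, growth and metabolic status are measured years after the 18- and 28-week exposure, and the protocol itself calls them intermediate. Holding them fixed blocks whatever part of the association runs through them. The remaining coefficient answers a narrower question than whether maternal status in pregnancy is associated with adult outcomes. Head circumference makes this plainest. The hypothesis runs through impaired brain development, and childhood head growth is a plausible proxy for that pathway.

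Conditioning on an intermediate can also link the exposure to unmeasured causes shared by that intermediate and the outcome. Childhood infection is an example: the Introduction names it as a postnatal influence, but it is neither in the list of controls nor in Table 1.

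A null result from such a model could be read as no long-term association, in a study meant to inform public health action. A related but secondary question arises for MRI: a model that removes intracranial volume does not directly test a global reduction in brain volume.

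**Working it through.** **1. Roles given to each variable**

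| Variable in the objective's control list | Role elsewhere in the article | Shown to follow the exposure? |
|---|---|---|
| Offspring nutrition | Intermediate (Data management) | Treated so by the protocol |
| Growth and development, including head circumference | Intermediate (Data management) | Treated so by the protocol |
| Metabolic status | Intermediate (Data management); associated with the maternal pattern at 6 years (Introduction) | Treated so, with a reported association |
| Education | Table 1 lists mother's and father's education only | No; parental education is a plausible confounder |
| ACE | Socioenvironmental variable (Table 1) | No |

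The conflict therefore concerns three items of the list, not all five.

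**2. The protocol's own power figure**

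Inputs from Power estimation: slope 0.11 SD per SD, n=550, 5% level (sidedness not stated), claimed power 80%. With the Fisher z approximation, power = Φ(atanh(r)·√(n−3) − z).

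- Two-sided: atanh(0.11) = 0.1104 and √547 = 23.39, with product 2.583. Then 2.583 − 1.960 = 0.623, and Φ = 73.3%.
- One-sided: 82.6%.

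The stated 80% is not reproduced exactly. That is a separate matter, and the present point does not depend on it. The baseline below is 73%.

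**3. Illustration of the loss**

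Assumptions: the total association is 0.11; a share m runs through the controlled variables in the same direction; there is no collider bias and no gain in residual variance from adjustment. Then adjusted slope = 0.11 × (1 − m). The documents give no value for m, so a range is shown. The second sample size is the 386 participants assessed by March 2020 (Current status section).

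| Assumed m | Adjusted slope | Power, n=550 | Power, n=386 |
|---|---|---|---|
| 0% | 0.110 | 73% | 58% |
| 10% | 0.099 | 64% | 49% |
| 20% | 0.088 | 54% | 41% |
| 30% | 0.077 | 44% | 33% |
| 50% | 0.055 | 25% | 19% |

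**4. Intracranial volume**

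Suppose the exposure groups differ by 0.3 SD in a regional volume and by a SD in intracranial volume, with within-group correlation ρ between the two. The adjusted difference is 0.3 − ρ·a.

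- a=0.1, ρ=0.4: 0.3 − 0.04 = 0.26.
- a=0.3, ρ=0.7: 0.3 − 0.21 = 0.09.

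Dividing by √(1 − ρ²) to allow for the reduced residual variance gives 0.284 and 0.126. With a=0.1 and ρ=0.7, the result is 0.23/0.714 = 0.322, slightly above the unadjusted 0.3. So adjustment costs little, or even helps, when head size barely differs between groups. It removes much of the signal when the effect is global. The values of a and ρ are assumptions.

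**The case against.** The strongest reply is that the objective is a single sentence, whereas the analysis section is the operative text. That section fits exposure models first and brings in life course variables afterwards as modifiers or mediators, which is close to the right order. It calls itself a broad scheme, and exact covariate sets are often left to a fuller plan. Nor does the protocol use the term total effect.

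Much of this stands. A reader might infer that the total association will never be estimated; the documents do not support that. What remains is that the only adjustment set attached to the objective contains the intermediates, and no confounder-only model is named to answer it. The univariate models do not fill the gap, because the Introduction attributes B12 deficiency partly to low socioeconomic status, and that confounding stays in.

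Other stronger readings also fail:

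- **Education and ACE as consequences of exposure.** Table 1 lists only parental education, and nothing shows ACE to follow from maternal B12.
- **The birth-weight finding as direct proof.** The Introduction describes "markers of low vitamin B_12_ status in the mother (high homocysteine) to be causally associated with low birth weight in the offspring", but birth size is outside the later-life list. It makes an effect on growth plausible and no more.
- **Bias necessarily toward zero.** This requires mediation in the same direction as the effect. Opposing mediation or collider bias could move the estimate either way.
- **Intracranial-volume adjustment as an error.** It is defensible for regional effects, and much of the imaging plan is regional.

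**Conclusion.** The concern holds as an inconsistency that affects what the primary result means. Offspring nutrition, growth and metabolic status are controls in the objective and intermediates elsewhere. Followed as written, the objective yields an estimate that is not the total long-term association. The exposure-first sequence mitigates this but does not settle which model gives the answer.

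The size of any loss cannot be derived from the documents. The fall from about 73% power to 44% or 25% at n=550 rests on assumed mediated shares of 30% and 50%, same-direction mediation, a two-sided test and no variance gain from adjustment. It shows what could happen and does not estimate it.

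The MRI point is secondary: the hypothesis of reduced brain volume lacks a test that leaves global volume differences in.

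**What to change.** Reword the first primary objective and name the model that answers it:

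- **Primary:** maternal B12, folate and their interaction, adjusted for pre-exposure or concurrent factors (parental education, standard of living index, preconceptional maternal size, other maternal nutrients) plus offspring sex and age.
- **Mediation or modification:** offspring nutrition, growth and metabolic status, and the offspring's own education if that is what the objective means. State which education variable is intended.
- **ACE:** keep as a covariate, or examine in a sensitivity analysis.
- **Secondary:** retain the fully adjusted model, labelled as conditional on later-life variables.
- **Objective 2:** add a test of total brain or grey matter volume without intracranial volume, and keep the adjusted model for regional effects.

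The cost is rewording, model order and one further imaging comparison. The variables are already held or being collected, so no new measurements are needed.
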